**Co-interventions::**

Further chemotherapy will be offered to patients as per current practice.

Outcomes

Pilot study: Patients and clinicians’ acceptability of the trial to assist in optimization of recruitment.

Primary outcome: One-year overall survival (OS).

Secondary outcomes: Progression-free survival (PFS), adverse events.

Follow-up: One-year follow-up for OS.

Sample size: Twenty patients to demonstrate therapeutic effect of peritoneal effusion caused by OC.

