## 2. Design

This clinical trial is a single-center exploratory single-arm study approved by the Ethics Review Committee of Zhongshan Affiliated Hospital, Guangzhou University of Chinese Medicine (Approval Number: 2021ZSZY-LLK-163). The trial is registered at chictr.org.cn (ChiCTR2100045155, May 7, 2021). The trial will be conducted in accordance with the Declaration of Helsinki (64th version, October 2013) and the guidelines for Good Clinical Practice (GCP). The in-and exclusion criteria are summarized in Table 1.

**Table 1 T1:** In- and exclusion criteria.

Inclusion criteria	Exclusion criteria
Pathologically or cytologically confirmed ventral or pelvic malignancy, positive peritoneal metastasis of these cancer or positive exfoliated cells of these cancer were detected in peritoneal lavage fluid	Drug allergy history of TNF and its derivatives
Moderate or greater amount of peritoneal effusion. Definition of moderate ascites, ultrasonic examination of ascites in decubitus position (≥3 cm); accompanied with clinical symptoms (abdominal distension and discomfort)	Pregnant or lactating women, women of child-bearing age who were not willing to use contraception during the study period; or men are unwilling to use effective contraceptives during treatment and for the next year
Aged 18‐75 years male or non-pregnant or lactating women	Patients with severe or uncontrolled medical diseases and infections (including atrial fibrillation, angina pectoris, cardiac insufficiency, ejection fraction less than 50%, uncontrollable hypertension, body temperature > 38 °C, etc)
Bone marrow reserve function is good, blood routine meets the following conditions: white blood cell (>3.5 * 10^9/L), neutrophil (>1.5 * 10^9/L), platelet(>100 * 10^9/L), hemoglobin (>90 g/L)	Encapsulated peritoneal effusion
Good organ function, biochemical examination met the following conditions: ALT < 2.5 * ULN, AST < 2.5 * ULN, serum total bilirubin < 1.5 * ULN, serum creatinine < 1.5 * ULN	Severe hypoproteinemia
ECOG <= 1	HIV positive and active hepatitis
Voluntary signing of informed consent	Patients with severe or uncontrollable mental illness
	Any condition that is unstable or that could jeopardize the safety of the subject and their compliance in the study

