### 2.1. Start trial

Inclusion, treatments started in Zhongshan Affiliated Hospital, Guangzhou University of Chinese Medicine by the end of 2021. Twenty patients will be enrolled in this trial.

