### 2.5. Statistical analysis

SAS 9.4 statistical analysis software is used for calculation. Full analysis set (FAS) refers to the case that has used the research drug at least once and has at least 1 main index measurement data after treatment. For the case data of failure to observe the whole treatment process, the last observation data is used to carry forward to the final result last observation carried forward (LOCF) of the study. Cases never using the drug of this study will be excluded. Per Protocol Set (PPS) refers to the case that meet the inclusion criteria, do not meet the exclusion criteria, have valid baseline values, have good compliance, and do not violate the clinical trial protocol (e.g., do not use prohibited drugs, etc), on the basis of the FAS. Safety Set (SS) refers to the case that has used the study drug at least once after enrollment and have a record of safety indicators. Both the full analysis set and the protocol set were used in the efficacy analysis, and FAS results were the main results. Security analysis uses security data sets. The statistical or grade data is compared by *χ*^2^ test and two-category Logistic multiple regression (Enter method) to analyze the factors affecting the objective curative effects. *P* < 0.05 are considered as statistically significant difference.

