Multiple studies have shown that rmhTNF-NC achieved excellent results in local treatment of advanced-stage thoracic and abdominal effusion. A prospective, open, single-arm, large-sample, multicenter phase IV trial involving 985 patients with rmhTNF-NC for monotherapy perfusion for malignant thoracic and abdominal effusion showed that the ORR of 916 patients after treatment was 62.44%, and the DCR was 97.27%. The ORR of malignant pleural effusion group was 70.52%, and that of malignant abdominal effusion group was 46.03%.^[30]^ A meta-analysis involving 694 patients from 12 studies revealed that pleural infusion of rmhTNF-NC combined with cisplatin increased ORR and improved QoL in patients with malignant pleural effusion.^[27]^

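### The claim that twenty patients demonstrate a therapeutic effect has no analysis behind it: the methods stated for this single-arm trial relate patient factors to response, and none estimates, bounds or tests the ORR

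*Protocol article*

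**What the plan says.** The Design section states: "This clinical trial is a single-center exploratory single-arm study". The Introduction likewise describes a single-arm phase I trial meant to explore efficacy. There is no control group.

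Section 2.4 makes effectiveness against abdominal effusion the primary objective. It defines the ORR as complete plus partial responses and the disease control rate as those plus stable disease. The abstract instead names one-year overall survival as the primary outcome.

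On size, section 2.1 says "Twenty patients will be enrolled in this trial", and the abstract gives the purpose: "Sample size: Twenty patients to demonstrate therapeutic effect of peritoneal effusion caused by OC".

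Section 2.5 sets out the software, three analysis sets, a carry-forward rule and the inferential methods. On the last it says "The statistical or grade data is compared by *χ*^2^ test", adds a binary logistic regression for factors affecting the objective response, and closes with "P* < 0.05 are considered as statistically significant difference". It does not say what the chi-square test compares with what, or whether P is one- or two-sided.

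The only historical ORR for abdominal effusion is in the Discussion. In a phase IV study of rmhTNF-NC given alone, "that of malignant abdominal effusion group was 46.03" per cent. The article cites this as background and does not link it to the analysis.

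**The concern.** Three statements do not fit together. The trial has one arm, the named tests look for differences or associations between patients, and the sample is said to be enough to demonstrate a treatment effect. An association between, say, tumour type and response says nothing about whether the regimen works. Whether it works, in a one-arm trial, is a question about the size of the ORR and its uncertainty.

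Followed as written, the trial would report an ORR without an interval, alongside P values that answer another question. A small P value from a factor analysis could then be read as evidence of efficacy. The risk is real here: the article's Conclusion already calls the combination effective and announces a multicentre randomised trial to follow.

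**Working it through.** **1. Can N = 20 be reproduced?** No. The article gives no null rate, target rate, power, sidedness, precision or dropout rate. The figure can be neither confirmed nor refuted from the article's own inputs.

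**2. What each stated method answers.**

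| Stated method | Question it can answer in one arm | Speaks to the ORR itself? |
|---|---|---|
| Chi-square comparison | Does response differ between patient subgroups? | No, unless a reference rate is named, and none is |
| Binary logistic regression | Which factors are associated with response? | No, as its purpose is stated |
| P < 0.05 | Significance level for the two above | No |

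**3. What twenty patients can estimate.** Input: n = 20, assuming all twenty enter the full analysis set. For x responders the Clopper-Pearson 95% limits are

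- lower = 0.025 quantile of Beta(x, 20 − x + 1)
- upper = 0.975 quantile of Beta(x + 1, 20 − x)

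| Responders | ORR | Exact 95% CI |
|---|---|---|
| 10/20 | 50% | 27.2% to 72.8% |
| 14/20 | 70% | 45.7% to 88.1% |
| 15/20 | 75% | 50.9% to 91.3% |

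The interval is widest at 10/20, where its half-width is (72.8 − 27.2)/2 = 22.8, or about 23 percentage points. Away from 50% the interval is asymmetric.

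**4. What demonstrating an effect would require (illustration only).** Assumption: the null rate is the background monotherapy figure, p0 = 46.03%. The article does not designate it as a null. For a rule of at least r responders, with X binomial(20, p):

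P(X ≥ r | p) = Σ from k = r to 20 of C(20, k) p^k (1 − p)^(20 − k)

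At p = 0.4603: P(X ≥ 13) = 0.0697, P(X ≥ 14) = 0.0267, P(X ≥ 15) = 0.0083.

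| One-sided level | Rule | Exact type I error | Power at ORR 70% | at 75% | at 80% |
|---|---|---|---|---|---|
| 0.025 | ≥ 15/20 | 0.8% | 42% | 62% | 80% |
| 0.05 | ≥ 14/20 | 2.7% | 61% | 79% | 91% |

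**5. The rule and the interval must match.** At 14/20 the two-sided 95% interval starts at 45.7%, which does not exclude 46.03%. A 14/20 rule paired with a 95% interval could therefore declare success while its own interval includes the benchmark. The 90% exact interval at 14/20 starts at 49.2% and is consistent with the one-sided 0.05 rule. At 15/20 the 95% interval starts at 50.9% and is consistent with the one-sided 0.025 rule.

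**The case against.** The strongest reply is that this is a condensed article. An interval method or a one-sample test is commonly left to the analysis plan, and an exploratory study needs no success threshold. That stands as far as it goes, and the absence of such detail is not the point. The point is a mismatch in what is stated: a one-arm exploratory design, methods that examine factors, and a sample said to demonstrate an effect. A fuller analysis plan could supply an interval, but the published methods would still not support the published claim.

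A reader might infer several stronger things that the article does not support.

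- *That chi-square and logistic regression are invalid without treatment arms.* Both can relate patient factors to response within one arm, which is the use given for the logistic model. A one-sample chi-square can also test a single proportion, but only against a stated reference, and none is given.
- *That twenty patients are too few to demonstrate anything.* The missing element is the benchmark and rule, not the number. Under the assumed null, power reaches 79% at a true ORR of 75% (one-sided 0.05) and 80% at 80% (one-sided 0.025).
- *That 46.03% is the trial's null rate.* It is a monotherapy rate cited as background, while the regimen here adds cisplatin HIPEC. Choosing it as the null would be a decision for the sponsor to justify.
- *That chi-square should simply be replaced by Fisher's exact test.* With ten patients in each group and 46% responding, the expected responder count is 10 × 0.46 = 4.6, just under the usual 5. For 10:10, 6:14 and 4:16 splits at response rates of 46% to 80%, however, the actual type I error is about 3% to 5.4% for chi-square and about 1% to 3% for Fisher. That is a trade-off, not an error in the plan.

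**Conclusion.** Wrong as written, in a limited sense. The stated methods do not address the section 2.4 objective, and the abstract's claim that twenty patients demonstrate a therapeutic effect has no analysis or decision rule behind it and conflicts with the exploratory label. The mismatch rests on the article's text alone and needs no assumed benchmark.

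On size, twenty evaluable patients support an estimate with a half-width of up to about 23 points. Whether they could also support a demonstration depends on a null rate, sidedness and threshold that the article does not give. With 46.03% as an assumed null, power at a true ORR of 70% to 80% runs from 42% to 80% at one-sided 0.025 and from 61% to 91% at one-sided 0.05. All figures assume twenty patients in the full analysis set and would weaken with fewer.

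**What to change.** 1. First reconcile the primary outcome, which is one-year overall survival in the abstract and effusion response in section 2.4. No rule or precision statement can be fixed until that is settled.
2. In section 2.5, make the main effusion analysis the ORR in the full analysis set with an exact (Clopper-Pearson) 95% confidence interval.
3. Restate the sample-size line along these lines: twenty patients to estimate the ORR, with an exact 95% interval of half-width at most about 23 percentage points (27% to 73% at 10/20).
4. Label the chi-square and logistic factor analyses exploratory, and say that they are not evidence of a treatment effect.
5. If the sponsor prefers to keep the claim to demonstrate an effect, prespecify and justify a null rate, state the sidedness, and set a threshold that agrees with the reported interval. Under the illustrative null, that means 15/20 with a 95% interval or 14/20 with a 90% interval.

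The cost is text only, with no extra patients for items 1 to 4. The price is a less favourable claim. Under item 5 the sponsor would also have to accept the power that twenty patients give for the null it chooses.

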### 2.4. Primary and secondary objectives

Primary objectives: HIPEC effectiveness in the combined treatment of rmhTNF-NC in abdominal effusion caused by advanced OC will be analyzed. The response will evaluated according to the WHO criteria^[9]^ and will classify as complete response (CR): the abdominal effusion disappeared completely and lasted for more than 4 weeks, partial response (PR): more than 50% less effusion than before treatment (based on the maximum depth of effusion observed by B-ultrasound examination), stable disease (SD): fluid accumulation should be reduced by less than 50% or increased by less than 25% from before treatment (based on the maximum depth of fluid accumulation observed by B-ultrasound examination), and progressive disease (PD): Fluid accumulation increased by more than 25% compared with before treatment. Objective response rate (ORR) calculated by CR + PR. Disease control rate (DCR) calculated by CR + PR + SD. The evaluation of adverse reactions was divided into grade 0 to 4 according to NCI CT CAE 4.0.

Secondary objective: Quality of life (QoL), QoL was assessed with the European Organization for Research and Treatment for Cancer Quality of Life Questionnaire core 30 (EORCT QLQ-C30) by the dietician before HIPEC and 1 month after HIPEC.

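### The forced-entry multiple logistic regression has at most 5 events per covariate in 20 patients, so its odds ratios will be unstable and its P values unreliable

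*Protocol article*

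**What the plan says.** Section 2.5 of the protocol article names two methods for categorical data: a chi-square test and a "two-category Logistic multiple regression (Enter method) to analyze the factors affecting the objective curative effects". The Enter method puts every chosen covariate into one model at once. One threshold covers all tests: P values "< 0.05 are considered as statistically significant difference". The outcome is objective response, defined in section 2.4: "Objective response rate (ORR) calculated by CR + PR". It is therefore binary.

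The sample size is fixed in section 2.1: "Twenty patients will be enrolled in this trial". The abstract gives the only rationale: "Twenty patients to demonstrate therapeutic effect of peritoneal effusion caused by OC". Section 2 describes a "single-center exploratory single-arm study", so the regression has no treatment term and can concern only patient or disease factors.

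The article does not list covariates, and it does not say whether Wald or likelihood-ratio tests will be used. An article may leave both to a fuller document, and neither omission is the point here. The point is that a forced-entry multiple model is paired with 20 patients, and the text itself fixes that pairing.

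**The concern.** The information in a logistic regression is limited by the size of the rarer outcome class. With 20 patients that class is small, and forcing several covariates in together spreads it thinly. Three things can follow:

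- Ordinary maximum-likelihood odds ratios scatter widely and are biased away from 1.
- A combination of covariates may split responders from non-responders perfectly or almost so (separation), and then no finite estimate exists.
- Large-sample P values no longer hold their nominal level, in a direction that depends on the test.

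At stake is any published statement about which factors affect response. Section 4 announces a multicentre randomised trial as the next step. The article does not say that predictor results would shape that trial, but inflated or false predictors would then be on record.

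**Working it through.** **Inputs.** N = 20 (section 2.1). The outcome is CR + PR, yes or no (section 2.4). The significance level is 0.05 (section 2.5), taken as two-sided. The only response rate the article cites for abdominal effusion comes from a single-agent study: "that of malignant abdominal effusion group was 46.03" per cent (section on recombinant mutant human TNF). No response rate is stated for this trial, so 46% to 70% is assumed, with 80% as a further case. The number of covariates, k, is not given and is varied. No power or effect size is stated for the regression, so there is no planned figure to reproduce.

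**Step 1: upper bound, no simulation needed.** The rarer class is min(responders, non-responders) and cannot exceed 20 / 2 = 10. A multiple model has k of at least 2. Events per covariate therefore cannot exceed 10 / 2 = 5.

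**Step 2: expected events per covariate.** This is E[min(X, 20 − X)] / k, with X binomial (20, response rate).

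| Response rate | Expected rarer class | k = 2 | k = 3 | k = 5 |
|---|---|---|---|---|
| 46% | 8.13 | 4.1 | 2.7 | 1.6 |
| 70% | 5.95 | 3.0 | 2.0 | 1.2 |
| 80% | 4.00 | 2.0 | 1.3 | 0.8 |

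Above 50%, a better treatment makes the model weaker, because non-responders become the rarer class. Twenty is also a ceiling: the full analysis set drops patients without a post-treatment measurement, and efficacy is analysed again in the per-protocol set.

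**Step 3: simulated error rates.** The setting is N = 20, independent covariates (a mix of binary and continuous) with no true effect, and response rates of 46% and 70%. Separation was checked by linear programming. Error rates are among fits that can be estimated. The multiplicity baseline is 1 − 0.95^k, the rate for k independent valid tests.

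| | k = 2 | k = 4 | k = 6 |
|---|---|---|---|
| No finite estimate | 3% to 10% | 7% to 18% | 15% to 35% |
| Any false factor, likelihood-ratio | not used here | about 26% | 35% to 42% |
| Multiplicity alone | 10% | 19% | 26% |

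Wald tests flagged any false factor in about 3% to 7% of trials. Under the likelihood-ratio test, small-sample failure adds about 26 − 19 = 7 percentage points with four covariates and 35 − 26 = 9 to 42 − 26 = 16 with six. Under Wald, the rate is well below the multiplicity baseline because the standard errors are inflated.

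Separate runs agree to within a few points. At an 80% response rate they give no finite estimate in 37% of trials with three covariates and 48% with five. With all-continuous covariates separation is rarer: 0.5% to 2% with three covariates and 2.5% to 11% with five, at 46% to 70%.

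**Step 4: size of the odds ratios.** With four continuous covariates, a true odds ratio of 2 and a response rate near 50%, the median estimate is 2.6. On the log scale that is ln 2.6 / ln 2 = 0.956 / 0.693 = 1.38, or 38% too large. With no true effect, the typical size of an estimated odds ratio (the exponential of the mean absolute coefficient, mixed covariates, k = 3 to 8) is 2.0 to 3.6. That second figure measures scatter rather than bias.

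**The case against.** Four arguments can be made for leaving the plan as it is.

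1. **The covariate list may sit elsewhere.** This is fair, and its absence is not held against the article. But the bound of 5 in step 1 holds for every list with two or more covariates.

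2. **The harm depends on the test and on the covariates.** This stands. A reader might infer that the model is bound to produce spurious significant factors or fail to converge, and that any factors reported would be mostly noise. The documents do not support that. With two to four covariates, at least 82% of simulated fits (100 − 18) are estimable at response rates of 46% to 70%. Most estimable null fits show no significant factor even under the likelihood-ratio test. Under Wald tests false positives are uncommon. The share of significant findings that would be noise cannot be computed, because nothing is known about true effects.

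3. **Part of the likelihood-ratio error is ordinary multiplicity.** This is also correct: 19% of the 26% with four covariates. The excess due to small numbers is real but smaller than the raw figure suggests.

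4. **The study is exploratory and the regression is not its main result.** The second half stands: the response rate is estimated without the model. The first half helps less. Section 2 applies the word to the study, but section 2.5 attaches a significance threshold and does not label the regression descriptive.

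What remains is that neither test gives a usable answer. One flags too many factors. The other has little chance of detecting a real one.

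**Conclusion.** The point holds as a should-fix matter. A forced-entry multiple model in at most 20 patients has at most 5 events per covariate, and about 4 with two covariates or 1.6 with five at the cited response rate. Its odds ratios will be unstable and biased away from 1. It may have no finite estimate, in roughly 3% to 35% of trials for 2 to 6 mixed covariates and a response rate of 46% to 70%. Depending on the unstated test, it gives either excess false positives or conservative, low-powered results with very wide intervals.

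The bound of 5 is certain. The percentages rest on independent covariates, a two-sided 0.05 level, and an assumed covariate mix and response rate. Whether a given analysis would fail, or yield a false predictor, cannot be said from the article. The primary response-rate estimate is unaffected.

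**What to change.** In section 2.5, replace the Enter-method model with a sentence stating three things: the objective response rate will be shown with an exact confidence interval by two or three baseline factors named in advance (for example primary tumour, baseline effusion depth and ECOG status); the display is descriptive; and the P < 0.05 rule does not apply to it. The intervals will be wide. Even 9 responders among all 20 patients give an exact 95% interval of 23% to 68%, and subgroup intervals will generally be wider still, which shows the reader how little can be concluded.

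If a model is wanted, fit one factor at a time with Firth-penalised or exact logistic regression, label it exploratory, and note that several factors are examined. Ordinary maximum likelihood is not safe even then: with a single binary factor, the simulation found no finite estimate in 2%, 8% and 21% of trials at response rates of 46%, 70% and 80%.

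The cost is one sentence and less analysis work. The loss is that no adjusted odds ratios can be reported, and 20 patients cannot support them reliably.

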### 2.3. Follow-up

During follow-up before and after the completion of HIPEC, physical examinations and measurements of white blood cell count, Hemoglobin, neutrophil count, blood platelet count, liver enzymes and serum creatinine levels were performed and then every 1 month for abdominal ultrasonography until the one-year point.

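### In a 20-patient study the factor analysis uses only a yes/no response cut from a measured ultrasound depth; this discards information, by an amount that depends on inputs the protocol does not give

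*Protocol article*

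**What the plan says.** The protocol article describes a "single-center exploratory single-arm study" (section 2) and says "Twenty patients will be enrolled in this trial" (section 2.1).

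Section 2.4 builds the response classes on effusion depth. PR is "more than 50% less effusion than before treatment (based on the maximum depth of effusion observed by B-ultrasound examination". CR requires that "the abdominal effusion disappeared completely and lasted for more than 4 weeks". The two are then pooled: "Objective response rate (ORR) calculated by CR + PR".

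Section 2.5 names the factor analysis: a chi-square test for categorical or graded data and "two-category Logistic multiple regression (Enter method) to analyze the factors affecting the objective curative effects". The significance rule is P "< 0.05 are considered as statistically significant difference".

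Depth itself is available. Table 1 requires at least 3 cm of ascites on ultrasound at entry. Section 2.3 schedules scans "every 1 month for abdominal ultrasonography until the one-year point". Section 2.5 admits a patient to the full analysis set only with at least one post-treatment value of the main index. The only factor analysis described is on the categorised response.

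**The concern.** Responder status is a cut on a measurement. A 49% and a 51% reduction become opposite outcomes, while a 51% and a 95% reduction become the same one. A factor that shifts depth across its whole range shows in the model only through patients who cross the cut.

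With 20 patients this matters in two ways. A real factor is harder to detect, and the result can turn on one or two patients near the cut. The loss is present even with a single factor, so it is separate from how many covariates the model can carry. The reported ORR, DCR and safety results are not affected.

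**Working it through.** **Plan's own figure.** There is none to reproduce. The 20 patients come with no effect size, power or formula, and the factor analysis has no stated power.

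**Inputs from the article.** N = 20, single arm; level 0.05 (two-sided assumed); response = CR + PR, cut at a 50% depth reduction. Background response rates in section 3.2 are 46.03% (abdominal effusion) and 62.44% (thoracic and abdominal together). They are not design assumptions of this trial. They imply 20 × 0.4603 = 9.2 or 20 × 0.6244 = 12.5 responders.

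**Inputs assumed.** A two-level factor splitting patients 10 v 10; after/before depth ratio log-normal with SD 0.6 on the log scale; ratios below 25% read as zero; median ratio m = 0.37, 0.50 or 0.65; group difference d in log-SD units.

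**Formulas.** Group response rate = Φ([ln 0.5 − ln m]/0.6 ± d/2). With m = 0.50 this is Φ(±d/2): 69% v 31% at d = 1.0, 73% v 27% at 1.2 and 77% v 23% at 1.5. Loss = power of rank-sum on the depth ratio − power of uncorrected chi-square on response.

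**Simulation (ranges over the three medians).**

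| d (SD) | Chi-square | Rank-sum | Loss (points) |
|---|---|---|---|
| 0.3 | low | low | 1-2 |
| 0.5 | 11-13% | 16-18% | 4-6 |
| 0.8 | – | – | 7-13 |
| 1.0 | 33-38% | 50-51% | 12-20 over 1.0-1.5 SD |
| 1.2 | 46-52% | 66-67% | as above |
| 1.5 | 63-71% | 83-86% | as above |
| 2.0 | – | – | 6-10 |

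With no effect, chi-square rejects in 3-4% of trials and rank-sum in 4-5%, so the gain is not bought with extra false positives.

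**Cross-check by exact calculation.** Noncentral-t power for a normal depth change against enumerated chi-square power after cutting the same variable at the overall ORR, 10 v 10:

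- ORR 46.03%: 18.5 − 12.5 = 6.0 points at d = 0.5; 39.5 − 26.1 = 13.4 at 0.8; 56.2 − 38.3 = 17.9 at 1.0; 80.0 − 59.8 = 20.2 at 1.325; 98.8 − 91.2 = 7.6 at 2.0.
- ORR 62.44%: 6.9, 15.3, 20.8, 24.3 and 11.6 points at the same five values of d.

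**Uneven factor, 14 v 6.** The rank-sum comparison gives about 0-22 points depending on ORR. The t-test comparison at ORR 46% gives 14.5, 20.5 and 28.1 points at d = 0.8, 1.0 and 1.5.

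**The multivariable logistic model.** Assumptions: normal covariates, slope 0.5 SD of depth change per SD of the tested covariate, ORR 46%, Wald tests, 600 simulations, non-converged or separated fits counted as non-significant. Power with 1, 3 and 5 covariates is about 22%, 15% and 5%, against 52%, 48% and 41% for linear regression on depth. The loss is about 31-36 points (the rounded figures subtract to 30, 33 and 36). Part of it comes from the Wald test and from separation with about 9 responders, not from the cut alone.

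**The case against.** The strongest case for leaving the plan alone has five parts.

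- **The cut buys something.** CR + PR is the trial's own response endpoint, it can be set beside the published 46.03%, and the logistic model speaks directly to it. CR also carries persistence beyond 4 weeks, which depth at one scan does not. This stands. A reader might infer that the cut costs power for no return; the article does not support that.
- **The loss is not a known quantity.** A reader might infer a fixed loss of 13-20 points. The article gives none of the inputs. That range belongs to large factor effects, where one factor moves response from roughly 31% to 69% or more. At 0.5 SD both tests have little power and the loss is 4-6 points. This stands.
- **Chi-square is not the whole plan.** Section 2.5 attaches it to categorical or graded data, so it may be meant for the four ordered classes. The chi-square figures therefore illustrate the cost of the cut and do not measure the logistic model. This stands; the model's own loss was larger under the assumptions shown.
- **Depth may be summarised elsewhere.** The article is condensed and the SAP is not shown, so it cannot be said that depth is never analysed. This stands. The point rests only on the method the article does state for factors.
- **A depth analysis needs definitions that are missing.** Section 2.2 drains ascites before treatment, so the baseline could be before or after drainage, and no response visit is fixed. This stands and makes the fix more than a change of test. The PR class already depends on the same two choices.

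**Conclusion.** The point holds as a conditional one. The stated factor analysis reduces a measured depth to a binary response, and in 20 patients that discards information. For a 10 v 10 factor the cost against a rank-sum test is about 1-6 points at 0.3-0.5 SD, 7-13 at 0.8 SD, 12-20 at 1.0-1.5 SD and 6-10 at 2.0 SD. It is about 31-36 points for the multivariable logistic model at a slope of 0.5 SD, not all of it due to the cut. Every figure rests on assumed effect, spread and split.

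A reader might also infer that analysing depth would make the factor analysis adequate. It would not: 80% power needs a difference of roughly 1.3-1.5 SD (the t-test reaches 80.0% at 1.325 SD; rank-sum passes from 66-67% at 1.2 SD to 83-86% at 1.5 SD). The change is worth making because it uses existing scans, but it concerns an exploratory analysis only.

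**What to change.** In section 2.5:

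1. Keep ORR and DCR as the reported response endpoints.
2. For the exploratory factor analysis, make the main outcome maximum depth at one prespecified response visit as a percentage of depth at a stated baseline scan, with complete disappearance scored 0. Say whether that baseline scan is before or after drainage.
3. Analyse it with rank-based methods (rank-sum for two-level factors, Spearman correlation for continuous ones) or a regression with one or two prespecified factors. Report estimates with 95% CIs.
4. Show the binary response analysis as a supplement.

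Cost: a few sentences, since the baseline scan and the visit must be defined first, and a little programming. No new patients are needed, and the monthly scans are already scheduled. What is given up: the main factor result is on depth change and not an odds ratio for response, and it does not carry the duration element of CR. The supplementary binary analysis keeps both in view.
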